## Abstract

**Background:**

Critical care nursing in Zambia is a new speciality that has adopted traditional nursing documentation and currently uses the Roper, Logan and Tierney's Activities of Daily Living combined with NANDA International (NANDA‐I) criteria. It is a cause for concern that these models are based on different high‐income domains and are not critical care or context‐specific, making integration and application in practice challenging. Therefore, there is an urgent need to develop a Zambian context‐specific critical care nursing framework.

**Aims:**

This study aims to explore intensive care nurses' perceptions of the applicability of currently used nursing models and theories and to develop a new Zambian critical care nursing framework based on the principles of Ubuntu.

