**Methods:**

This study will employ a two‐phase, mixed‐methods approach using a participatory cooperative inquiry design. Phase 1 includes a retrospective review of nursing care plan documentation. This will allow for the identification of the current use of nursing models and theories. Phase 1 utilises documentary data analysis to identify key nursing documentation. Descriptive statistics and, where possible, significant difference will be used to determine patterns and trends. Phase 2 will utilise the findings from phase 1 as the basis for semi‐structured focus groups with intensive care nurses within the study site. Total population sampling will be used; therefore, all nurses will be invited to participate. Framework analysis will be used to analyse the qualitative data sets.

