**Conclusion:**

The outcomes will illustrate the efficiency and effectiveness of nursing documentation and perceptions of using the current nursing model. The findings will be combined to develop a critical care nursing framework based on Ubuntu, which will then be piloted.

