As Tierney [11, 12] has pointed out, nursing models did have their place in nursing. However, globally their use has continued to decline, with specialist nurses and new fields of nursing focusing on developing patient pathways for specific diseases and conditions [13]. This alternative approach is supported by Vieira et al.'s [14] critical review of the literature, which found that many previously accepted critical care models are outdated with few studies supporting their implementation, resulting in them remaining theoretical elements of education and training. In consequence, when discussing the challenges with stakeholders, they were clear that they wanted a Zambian context‐specific conceptual framework which could be operationalised within the current healthcare system. Carter's [8] Zambian study found that specialist critical care nurses in Zambia are deeply concerned that the current model of nursing is outdated and only seen as a theoretical part of their education. In practice, it is not fully understood by nurses (from student to MSc level) and has limited connection with critical care nursing or the African context. Therefore, it could be argued that for critical care nurses in Zambia to advance the nursing agenda, there is an urgent need to challenge the philosophies and courses that have been implemented in education and practice [15]. Thus, although it is accepted that Ubuntu philosophy was also not designed for critical care, nevertheless by definition its main concepts fit more nearly with Zambian familial and social patterns, making adaptation for application in intensive care possible.

When identifying possible philosophical frameworks, searches revealed the increasing recognition for Ubuntu across the African continent as offering an appropriate construct to build upon [16, 17, 18]. As Mugumbate and Chereni [19] point out, the key translation of ‘I am because we are’ typifies the way of life, the shared consciousness and interconnectedness that exist in African societies. The concepts inherent in this approach are therefore part of shared societal attitudes and would translate well into a context‐specific framework for critical care nursing service delivery. This would straddle both nursing strategies and patient and family needs and expectations, enabling the clinical care to be efficient, effective and culturally sound.

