## Aims

2

The interlinked aims of this study are to explore the knowledge and understanding critical care nurses have of the current nursing models officially, identifying positives, challenges and constraints. These will then be used to underpin the conceptualisation and development of a new context‐specific framework for critical care nursing based on the identified African philosophy of Ubuntu, and of direct applicability in Zambia.

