## Implications for Practice

6

Little has been published from low–middle‐income countries on context‐specific critical care nursing models and frameworks. However, as critical care nursing evolves and matures, it is important that context‐specific frameworks and models for practice are developed. Ubuntu has been identified as a possible context‐specific philosophy that can be translated for use in nursing care; however, it has not yet been applied to critical care nursing. Critical care in many low‐income countries is advancing, and this study is seen as a first step in the development of a context‐specific critical care nursing framework. Stakeholders (including the Ministry of Health and NMCZ) will play a key role in dissemination and implementation of the findings. They are keen to see processes developed that are culturally competent and will align practice to the needs of the population they serve. Also using participatory cooperative inquiry approach, future pilots of the new model will be led by stakeholders who have the research expertise to lead and guide such ventures.

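### As described, neither phase is set up to gather nurses' views on whether Ubuntu principles are workable in this ICU, or to count evidence against them

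*Protocol article*

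**What the plan says.** Two versions of the aim appear in the protocol article. The abstract (Aims) speaks of nurses' "perceptions of the applicability of currently used nursing models and theories". Section 2 (Aims) will "explore the knowledge and understanding critical care nurses have of the current nursing models officially, identifying positives, challenges and constraints". The abstract's conclusion gives the matching outcome: "perceptions of using the current nursing model". The abstract (Methods) links the phases: "Phase 2 will utilise the findings from phase 1 as the basis for" the focus groups, and Phase 1 is an audit of care plans for use of the current models.

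Ubuntu is settled beforehand. Section 2 wants the new framework to be "based on the identified African philosophy of Ubuntu, and of direct applicability in Zambia". Section 1 (Background) says "it is accepted that Ubuntu philosophy was also not designed for critical care", and argues that its concepts nevertheless suit Zambian family and social life well enough to be adapted. Section 6 (Implications for Practice) presents Ubuntu as a possible basis: "however, it has not yet been applied to critical care nursing".

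Ubuntu appears at two points in the analysis. Section 3.3 (Data Analysis) will search the transcripts for phrases that fit it. Section 4.1 (Development of the Framework) says the statistical analysis will also show how the current models differ from it.

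**The concern.** Evidence that the current models fit badly is not evidence that another basis fits well. The article faults the current models in part because they are not specific to critical care, and it accepts a similar limitation for Ubuntu. The basis with no record of use in critical care is thus the one that nurses are not stated to be asked about.

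The analysis leans the same way. A search for phrases that fit Ubuntu can add support but has no category for a remark that conflicts with it. At stake are the credibility of the intended direct applicability and protection against confirmation bias in choosing which elements enter the framework. Once the focus groups have been held, the gap can be filled only by reconvening the nurses.

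**Working it through.** No figure in the article bears on this point. The only calculated number, 92 care plan records, concerns the Phase 1 audit. The check is therefore a comparison of the places where nurses' views or Ubuntu enter the study.

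1. **What nurses are asked to judge.** Abstract aim: applicability of the current models. Section 2 aim: knowledge and understanding of the current models, with positives, challenges and constraints. Abstract outcome: perceptions of the current model. In all three places the object is the current models; in none is it Ubuntu.

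2. **What the focus groups start from.** They rest on Phase 1. Table 1 (Section 3.2) lists the audit content: patient details, written records, use of NANDA-I, use of the Roper, Logan and Tierney list, any other system found, and documentation standards. Ubuntu is not named as an audit item.

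3. **What the focus group tool contains.** Table 2 (Section 3.2) gives eight to nine questions with prompts. Their content is not shown, and the text says the tool is still to be developed, piloted and peer-reviewed.

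4. **How Ubuntu enters the analysis.** In Section 3.3 it is a pattern to be matched in the transcripts. In Section 4.1 it is a yardstick for the current models. In neither place is it assessed itself. Few matching phrases would tell little either, since silence from nurses who were not asked differs from a judgement that Ubuntu does not work.

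5. **What is conceded about Ubuntu.** It was not designed for critical care (Section 1) and is not yet applied there (Section 6). In the critical care row of Box 1, drawbacks are given for the Activities of Daily Living model and for NANDA-I, and none for Ubuntu.

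6. **What comes later.** Essential points are developed with stakeholders (Section 4.1), stakeholders review the model so that it can be refined (Section 5, Limitations), and piloting follows (abstract conclusion; Section 6). Section 3 (Design and Methods) counts two phases, the care plan review and the focus groups. Section 6 places pilots in the future, led by stakeholders. No criteria are stated for the review or the pilot, and both start from a framework already built on Ubuntu.

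**Extent.** Section 3.1.1 (Participants) gives 10 registered critical care nurses and a similar number of registered nurses, so 10 + 10 = about 20 participants. The point applies to all of them.

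**The case against.** The strongest reply has four parts.

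- **No comparison is promised.** The aims are to explore the current models and to develop a framework. A reader might infer that the study fails because it cannot show that the new framework applies better. The article does not support that: superiority is nowhere an aim, and direct applicability describes the framework to be built. The inability to show superiority limits what may be concluded; it is not a failed objective. This part stands.
- **Later checks exist.** A reader might infer that Ubuntu is never examined. That is also too strong, given the participatory design, development with stakeholders, their review and the pilot. Section 3.1 names the critical care nurses' association and ICU leadership among the stakeholders. What remains is that these steps follow the choice of Ubuntu and have no stated criteria.
- **The question schedule is not shown.** It may include Ubuntu, and using Phase 1 as a basis does not make it the only content. An article may leave the schedule to the full protocol. This stands, so the point cannot rest on absent questions. It rests on what is written: the two aims, the outcome and the direction of the transcript search.
- **Nurses' views on Ubuntu would be opinion.** They work with the current models, whereas Ubuntu is a philosophy and its critical care framework does not yet exist. Matched questions would set experience against expectation and could not prove a better fit. This stands as a limit on the fix. Opinions on where Ubuntu would not work remain useful when deciding what goes into the framework.

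The current models are also criticised on other grounds, such as their high-income origin and the difficulty of combining them, so lack of critical care design is one objection among several.

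**Conclusion.** The point holds in a limited form. As described, the two phases direct the nurses' assessment to the current models, take Ubuntu as given, and look in the transcripts only for what fits it. They are not set up to collect nurses' views on whether Ubuntu principles are workable in this ICU, or to let evidence count against them. The intended direct applicability would then rest on argument and on later steps without stated criteria.

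This is a worthwhile, inexpensive improvement and not a fatal flaw. It assumes that the unseen schedule follows the stated aims. If that schedule already asks about Ubuntu neutrally, what remains is to bring the aim and the transcript coding into line with it.

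**What to change.** - Extend the first aim, in the abstract and in Section 2, to cover nurses' views on the applicability of Ubuntu principles in critical care.
- Put this explicitly in the focus group schedule still to be developed (Section 3.2), in neutral wording and with a prompt on where the principles would not work. If Box 1 is used as a source for prompts, balance its Ubuntu column first.
- Change Section 3.3 so that transcripts are coded for phrases that conflict with Ubuntu as well as those that fit. Chart Ubuntu beside the two current models in the framework matrix.
- Report the Ubuntu elements that nurses judged unworkable.
- Limit the study's conclusion to development of the framework, and leave any statement that it applies better than the current models to the pilot.

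The cost is slightly less discussion time for each current model. No additional participants or phase are needed. Views on Ubuntu should be reported as opinion, not as experience of use.

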**Methods:**

This study will employ a two‐phase, mixed‐methods approach using a participatory cooperative inquiry design. Phase 1 includes a retrospective review of nursing care plan documentation. This will allow for the identification of the current use of nursing models and theories. Phase 1 utilises documentary data analysis to identify key nursing documentation. Descriptive statistics and, where possible, significant difference will be used to determine patterns and trends. Phase 2 will utilise the findings from phase 1 as the basis for semi‐structured focus groups with intensive care nurses within the study site. Total population sampling will be used; therefore, all nurses will be invited to participate. Framework analysis will be used to analyse the qualitative data sets.

**Conclusion:**

The outcomes will illustrate the efficiency and effectiveness of nursing documentation and perceptions of using the current nursing model. The findings will be combined to develop a critical care nursing framework based on Ubuntu, which will then be piloted.

**Relevance to Clinical Practice:**

This study has been designed in response to recognition that critical care nursing practice needs to context specific to enhance the nursing care provided.

## Background

1

Globally, critical care nursing is advancing with the result that survival from critical illness is increasing; however, survival in low‐income countries remains limited [1]. Zambia is classified by the World Bank [2] as a low‐ to middle‐income country with a GINI Index of 51.5%. Over the past decade, critical care nursing has been gradually advancing with the introduction of specialist nurse education programmes from diploma to master's level [3]. These changes are essential as critical care units are increasingly providing complex, high‐intensity, time‐specific care, with patients fully dependent on the expertise of the workforce. Key elements of good nursing care are the assessment, planning and implementation of care; for these to be effective, it is essential that they are specifically designed for use within the health system delivering the care. Clinical outcomes depend on rapid, effective responses to changes in patient status. Therefore staff systems that includes documentation that can be easily completed, is context‐specific and is applicable for the setting in which the unit is based [4, 5]. It is therefore an ongoing cause for concern that the current national model of critical care nursing in Zambia is based on the Roper, Logan and Tierney's Activities of Daily Living [6] and the NANDA International (NANDA‐I) (formerly, the North American Nursing Diagnosis Association) diagnosis criteria [7]. These two models were designed for two different, but high‐income countries and, in consequence, it is challenging to integrate them into any system, based on different philosophical assumptions and assessing different domains (Box 1). The situation is compounded because, as Box 1 illustrates, neither are critical care–specific nor designed for resource‐limited settings, and address different domains. To add to these technical differences, in no way do either of them reflect African philosophies of living and society [8]. Thus, when aiming to develop context‐specific critical care nursing care, nurses in Zambia are faced with a plethora of challenges when trying to apply these different principles to their practice [9, 10]. It is therefore perhaps not surprising that although the theory of these models is taught in student nurse education programmes and post‐qualifying higher‐level qualifications, there appears to be little application into practice. In addition, although Zambia has retained a focus on these nursing models, the limited published evidence on their use in resource‐limited settings, further demonstrating their lack of applicability.

**BOX 1 nicc70456-tbl-0001:** Similarities and differences between Roper, Logan and Tierney's Activities of Daily Living, NANDA‐I and Ubuntu.

	Activities of daily living	NANDA‐I	Ubuntu
Underpinning concepts	Person as an individual with functional needs.	Person as a responder to health problems	Person in relation to family, community and society
	Designed for Western settings	Designed for US settings	African philosophy and can be adapted to African nursing context
	Explicitly holistic about independence and focuses on physical, psychological, social and environmental	Holistic if the nurse selects diagnoses based on health problem	Holistic at a human and social level.
	Used to guide nursing care	Standardised nursing diagnoses	Guides nursing values and relationships with patients and families.
	Activity‐based framework	Taxonomy of diagnoses	Philosophical and ethical
	A person with varying levels of independence	A set of actual or potential human responses	A human being embedded in family, culture and community.
Use in critical care	Patients are often fully dependent. Not systems focused does not fit well with critical illness. Could be useful in critical care recovery.	Works well with protocols, documentation and multi‐disciplinary teams, which are challenging in resource constrained settings. Task centred and based on diagnoses.	Humanises critical care. Cultural and context‐specific ethical decision‐making structure with patient and family central. Built around a moral and ethical compass.

As Tierney [11, 12] has pointed out, nursing models did have their place in nursing. However, globally their use has continued to decline, with specialist nurses and new fields of nursing focusing on developing patient pathways for specific diseases and conditions [13]. This alternative approach is supported by Vieira et al.'s [14] critical review of the literature, which found that many previously accepted critical care models are outdated with few studies supporting their implementation, resulting in them remaining theoretical elements of education and training. In consequence, when discussing the challenges with stakeholders, they were clear that they wanted a Zambian context‐specific conceptual framework which could be operationalised within the current healthcare system. Carter's [8] Zambian study found that specialist critical care nurses in Zambia are deeply concerned that the current model of nursing is outdated and only seen as a theoretical part of their education. In practice, it is not fully understood by nurses (from student to MSc level) and has limited connection with critical care nursing or the African context. Therefore, it could be argued that for critical care nurses in Zambia to advance the nursing agenda, there is an urgent need to challenge the philosophies and courses that have been implemented in education and practice [15]. Thus, although it is accepted that Ubuntu philosophy was also not designed for critical care, nevertheless by definition its main concepts fit more nearly with Zambian familial and social patterns, making adaptation for application in intensive care possible.

When identifying possible philosophical frameworks, searches revealed the increasing recognition for Ubuntu across the African continent as offering an appropriate construct to build upon [16, 17, 18]. As Mugumbate and Chereni [19] point out, the key translation of ‘I am because we are’ typifies the way of life, the shared consciousness and interconnectedness that exist in African societies. The concepts inherent in this approach are therefore part of shared societal attitudes and would translate well into a context‐specific framework for critical care nursing service delivery. This would straddle both nursing strategies and patient and family needs and expectations, enabling the clinical care to be efficient, effective and culturally sound.

## Aims

2

The interlinked aims of this study are to explore the knowledge and understanding critical care nurses have of the current nursing models officially, identifying positives, challenges and constraints. These will then be used to underpin the conceptualisation and development of a new context‐specific framework for critical care nursing based on the identified African philosophy of Ubuntu, and of direct applicability in Zambia.

## Design and Methods

3

In line with the principle of Ubuntu, the study will use participatory cooperative inquiry throughout [20], as this approach with its shared ownership and focus on empowerment through shared multi‐directional learning is seen as essential. The aim is to empower critical care nurses and ultimately the Ministry of Health such that on the completion of the study, they take ownership of the findings of the study. This could then be translated for other specialist groups and nursing education programmes and could help align nursing care to the Zambian society. The study will have two phases; all steps of data collection and analysis will follow the guidelines for the method chosen, thereby re‐enforcing the context specificity, appropriateness and acceptability of processes used and all outcomes [21]. Figure 1 provides a schematic overview of the proposed research phases and development of the framework.

**FIGURE 1 nicc70456-fig-0001:**
[figure not shown]
Schematic overview of the proposed research phases and development of the framework.

Phase 1: Documentary data collection and analysis to compile a retrospective review of nursing care plans [22]. This will allow for the identification of the types of nursing problems identified, and on the use of the Roper, Logan and Tierny and NANDA‐I diagnosis, nursing plans and evaluation.

Phase 2: A series of focus groups with critical care nurses working in the intensive care unit (ICU). This will include both registered nurses and registered critical care nurses. Framework analysis will be used in this second phase as a core aspect of this approach to data collection and analysis is context checking, which will be conducted by co‐researchers' [23].

